### Outcomes

#### Primary Outcome

The primary outcome metric of the study is the OS period. OS is defined as the time after the start of any antitumor therapy for SMLC to death of any cause.

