## Methods

### Study Design

This study is a prospective cohort study. We will compare the treatment outcomes of surgical and nonsurgical methods for SMLC in a real-world clinical scenario. The study will enroll 240 patients (120 patients in the surgical group and 120 patients in the nonsurgical group) from June 1, 2022, to June 30, 2027. The patients will be visited postoperatively at 3, 6, 12, and 24 months. The study is due to be completed on June 30, 2029.

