### Patient Enrollment and Group Allocation

All patients with SMLC being treated at our center are potential candidates, and those who meet the inclusion and exclusion criteria will be eligible for enrollment in our study. Patients who receive surgical treatment along with postoperative systemic comprehensive treatment will be enrolled in the surgical group. Patients who receive only conservative treatment (eg, radiotherapy, chemotherapy, targeted molecular therapy, immunological therapy, etc) without surgical treatment will be enrolled in the nonsurgical group. All study procedures, as well as the participants’ rights, responsibilities, benefits, and risks, will be communicated, and participants will sign an informed consent form. Figure 1 displays the study flowchart.

In order to participate, patients will need to meet certain eligibility criteria. The inclusion criteria are (1) a pathological diagnosis of SMLC, (2) understanding and voluntarily participating in the study, and (3) being regularly followed up beyond 2 years or to the endpoint. Exclusion criteria include: (1) not receiving antitumor treatment at our hospital, (2) coexistence of spinal trauma or infection, (3) history of other malignancies, and (4) unwillingness to participate or inability to adhere to our follow-up schedule.

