### Treatment

A surgical decision is made following the advice of our institutional multidisciplinary treatment team for spinal metastasis. There are 3 indications for surgery at our center: severe yet drug-resistant local pain, progressive neurological dysfunction, and emerging or latent spinal instability. Otherwise, patients are referred for nonsurgical treatment.

In the surgical group, patients are given surgical treatment, neurological rehabilitation, and adjuvant therapies (ie, SBRT and antitumor drugs). In this setting, we have established a synchronized workflow for surgery-based multimodality therapy instead of the conventional step-by-step schedule. A synchronized workflow means that neurological rehabilitation is incorporated and commenced right before the surgery and that SBRT and antitumor drugs are started early and simultaneously during the process of rehabilitation.

In the nonsurgical treatment group, patients are treated with adjuvant therapies exclusively, including radiotherapy, chemotherapy, targeted therapy, immunological therapy, etc. Considering the existence of various adjuvant modalities, this study will only enroll patients who receive both locoregional radiotherapy and antitumor drugs.

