### Statistical Analysis

Statistical analysis will be performed using SPSS for Windows (version 20; IBM Corp). The Lilliefors test will be used to examine whether the data are normally distributed. Data will be presented as percentages, mean (SD), or median (range) accordingly. The 1-tailed unpaired Student *t* test and Pearson *χ*^2^ test (or the Fisher exact test) will be used to make comparisons between different groups. The OS and progress-free survival curves will be plotted using the Kaplan-Meier method, and a comparison of the two groups will be performed via the log-rank test. The influencing factors will be analyzed by univariate and multivariate Cox proportional hazards regression. Statistical significance is set at *P*<.05. The survival prediction model will be established by multivariate Cox regression models and the Kaplan-Meier survival curves. The predictive ability of the final model will be evaluated using the Harrell concordance index (C-index) and calibration curves.

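### Overall survival is counted from the first antitumor therapy, but the groups are defined by treatment received afterwards, so guaranteed survival time enters the primary comparison with unknown size and direction

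*Protocol article*

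**What the plan says.** Three parts of the Methods fix this point.

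- **Clock.** Primary Outcome: "OS is defined as the time after the start of any antitumor therapy for SMLC to death of any cause".
- **Groups.** Patient Enrollment and Group Allocation: "Patients who receive surgical treatment along with postoperative systemic comprehensive treatment will be enrolled in the surgical group". Patients given conservative treatment only, "without surgical treatment will be enrolled in the nonsurgical group". In its paragraph on nonsurgical treatment, the Treatment section adds that "this study will only enroll patients who receive both locoregional radiotherapy and antitumor drugs".
- **Analysis.** Statistical Analysis: Kaplan-Meier curves are drawn and "a comparison of the two groups will be performed via the log-rank test". Univariate and multivariate Cox regression follow. No landmark, delayed entry or time-dependent exposure is mentioned.

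Two further statements bear on timing. Surgery is decided on the advice of a multidisciplinary team, for "severe yet drug-resistant local pain, progressive neurological dysfunction, and emerging or latent spinal instability". In the surgical group, "SBRT and antitumor drugs are started early and simultaneously during the process of rehabilitation", with no interval given.

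The visit schedule is worded in two ways. Study Design says "The patients will be visited postoperatively at 3, 6, 12, and 24 months", whereas the Abstract counts the same visits from treatment.

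**The concern.** A survival comparison needs each patient's group to be known when the clock starts. Here it need not be. Someone who starts a drug and is operated on later belongs to the surgical group only by having lived until the operation, and then until the systemic treatment after it. The person-time before qualification is free of deaths by construction. Read literally, a patient who dies before the later required treatment falls out of the group that the treatment would have defined. A surgical candidate who dies before the operation might even be counted as nonsurgical.

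The nonsurgical group has its own qualifying wait, because both radiotherapy and drugs must have been received.

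The primary endpoint of the primary aim is at stake. Such a rule can produce a survival difference when surgery has no effect, or hide one that exists. Neither a larger sample nor adjustment for baseline covariates repairs a misaligned time zero.

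**Working it through.** **1. When is membership known?**

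| Patient | OS clock starts | Group known |
|---|---|---|
| Drugs or radiotherapy first, surgery later | first drug or radiotherapy | after surgery and postoperative systemic treatment |
| Surgery first, if surgery counts as antitumor therapy | surgery | after postoperative systemic treatment |
| Never operated | first modality | after the second modality, with no surgery |

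The first row can occur. No eligibility criterion excludes prior antitumor therapy, and drug-resistant pain or progressive neurological dysfunction can arise in a patient already on treatment. The synchronized workflow shortens the gap between surgery and adjuvant therapy. It does not shorten the gap between an earlier therapy and surgery.

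**2. The plan's own figure.** Sample Size and Study Timeline gives mean OS 11 (SD 4) and 9 (SD 3) months, α = .05 and β = .1. The mean variance is (16 + 9)/2 = 12.5, so n = 2 × 12.5 × (1.960 + 1.282)² / 2² = 65.7, or 66 per group, as stated. This point does not affect that figure; the 2-month difference is the yardstick below.

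**3. Illustration with no true effect, exponential survival, mean 9 months.** The delay from time zero to qualification is an assumption, because the article gives none. Take it as exponential with mean m, for surgical candidates only.

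- Mean OS of candidates who survive the delay: 9 + 9m/(9 + m).
- Share of candidates who die first: p = m/(9 + m), with mean survival 9m/(9 + m).
- If those deaths are dropped, the nonsurgical mean stays 9.
- If they are moved to the nonsurgical group (equal numbers of candidates and non-candidates), its mean is [9 + p × 9m/(9 + m)]/(1 + p).

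| m (months) | Surgical mean | Gap, deaths dropped | Nonsurgical mean, deaths moved | Gap, deaths moved |
|---|---|---|---|---|
| 1 | 9.90 | 0.90 | 8.26 | 1.64 |
| 2 | 10.64 | 1.64 | 7.87 | 2.77 |
| 3 | 11.25 | 2.25 | 7.65 | 3.60 |

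**4. The same with gamma survival, mean 9 and SD 3** (the article's nonsurgical figures; shape 9, scale 1). The share dying first is p = (m/(m + 1))⁹ and their mean survival is q = 9m/(m + 1). The surgical mean is (9 − pq)/(1 − p). The nonsurgical mean with deaths moved is (9 + pq)/(1 + p).

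| m (months) | p | Gap, deaths dropped | Gap, deaths moved |
|---|---|---|---|
| 1 | 0.002 | 0.01 | 0.02 |
| 2 | 0.026 | 0.08 | 0.16 |
| 3 | 0.075 | 0.18 | 0.34 |

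The bias almost vanishes because this distribution has very few early deaths.

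**5. Delays in both groups, and the effect on the test.** 2,000 simulated trials per scenario: 120 per group, no true effect, exponential survival with mean 9, censoring at 24 months, two-sided log-rank at .05. Delays are uniform from 0 to twice the mean, and deaths before qualification are dropped.

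| Mean delay, surgical / nonsurgical (months) | HR | False-positive rate |
|---|---|---|
| 0 / 0 | 1.00 | 5% |
| 1 / 0 | 0.90 | 12% |
| 2 / 0 | 0.81 | 36% |
| 3 / 0 | 0.75 | 62% |
| 2 / 1 | 0.91 | 12% |
| 1 / 1 | 1.00 | 5% |
| 0 / 1 | 1.12 | 13% |
| 0 / 2 | 1.23 | 36% |

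With gamma survival the rate was about 5–6% in every scenario and the spurious gain was at most about 0.1 months.

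**The case against.** Several counter-arguments have weight.

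- **Surgery probably counts as antitumor therapy.** The Background includes surgery in comprehensive treatment, Expected Findings equates comprehensive treatment with a combination of antitumor therapies, and Secondary Outcomes lists surgical complications under antitumor treatment. On that reading, surgery-first patients have no pre-surgery guaranteed time. This stands, and it shrinks the problem for them to the wait for postoperative therapy. It does not help patients treated with drugs or radiotherapy first, whose share is not given.
- **The delays are assumed, and exponential survival with mean 9 has SD 9, against the stated SD of 3.** This stands as a limit on size, so both cases are shown. An SD of 3 may be optimistic: the Background cites median survival after surgery from as low as 2 months to 14.
- **The group rule may describe intended treatment.** That is possible, since surgery follows a multidisciplinary decision. But the wording speaks of treatment received. A reader might infer that operative deaths will definitely be removed from the surgical group; the article does not state this, and it follows only from the literal reading.
- **Delayed entry or time-dependent methods may be in an unseen analysis plan.** This does not answer the point, because the article itself fixes both the OS origin and the group rules.
- **Visit clock.** A reader might infer from the postoperative wording that nonsurgical patients have no visit schedule. The Abstract gives them one, counted from treatment. The mismatch needs tidying but does not affect OS.

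**Conclusion.** The point holds as a structural fault. As written, time zero can precede the treatment that defines the group, and the stated analysis does not correct for it. It should be put right, because it concerns the primary endpoint.

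Size and direction cannot be read from the documents. The bias favours surgery if the surgical group's qualifying delay is the longer one, cancels if the delays are equal, and reverses if the nonsurgical delay is longer. With delays of 1 to 3 months in the surgical group only, the spurious gain runs from almost nothing (gamma, SD 3) to 2.3 months (exponential, deaths dropped) or 3.6 months (exponential, deaths moved), against a planned difference of 2 months. The upper figures assume that every surgical candidate starts another therapy first and that the nonsurgical group has no wait, so they are a worst case.

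A reader might infer that the rule favours the pro-surgery result anticipated in Expected Findings. It can do so, but the documents do not show that it will.

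**What to change.** Use one time zero for both groups: the date of the multidisciplinary treatment decision.

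- Classify each patient by the strategy decided on that date, and keep every enrolled patient in that group whether or not the later treatment follows.
- Count OS from that date. For patients already on therapy, record prior antitumor therapy and its duration, and adjust for both.
- Add a sensitivity analysis with surgery as a time-dependent covariate, or a landmark analysis.
- State whether surgery counts as antitumor therapy wherever that term is kept.
- Reconcile the visit wording in Study Design with that in the Abstract, so that both groups have the same visit origin.

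The cost is wording and one recorded date, which the described decision process should already produce. Enrollment is planned to June 2027, so the date can still be captured prospectively for patients yet to enter. It would have to be taken from records for those already enrolled. The small downside is that some patients will not receive the decided treatment, which slightly dilutes the as-treated contrast.

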#### Secondary Outcomes

Secondary outcomes include the following:

The progress-free survival period, defined as the time after the start of antitumor therapies until disease progression.Recovery of SMLC-related symptoms, defined as the relief of locoregional pain, which is measured by visual analogue scale (VAS) values, and the recovery of neurological status, which is assessed using the American Spinal Injury Association (ASIA) score. Immediate improvement in VAS and ASIA scores is assessed before discharge.Recovery of self-care performance, assessed using the Karnofsky Performance Scale (KPS) score and the Eastern Cooperative Oncology Group (ECOG) performance score.Quality of daily life, assessed by the Short Form 36 Health Survey Questionnaire.

Other outcomes for evaluation include complications in antitumor treatment. Surgical complications are rated according to the system proposed by Clavien et al [22], whereas toxicity of radiotherapy and antitumor drugs is graded using the National Cancer Institute’s Common Toxicity Criteria for Adverse Events (version 5.0). The endpoint of the study is the death of the recruited patient. The primary outcome is assessed by the endpoint of the study, whereas secondary and other outcome metrics are assessed at each visit.

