### Sample Size and Study Timeline

In this study, we plan to compare the overall survival (OS) time between the two groups and explore its prognostic factors. The sample size calculation was based on the survival time and estimation of influencing factors. According to an unpublished retrospective study performed at our center and previous literature [20,21], the average OS time was 11 (SD 4) months in the surgical group and 9 (SD 3) months in the nonsurgical group. Assuming an overall Type 1 error (α) of .05 and Type II error (β) of .1, we need 66 patients in each group. Additionally, there are 12 predictive factors we plan to analyze in the prediction model. According to the sample size estimation method for multivariable regression models, 100 cases in each group are needed (the ratio of surgical to nonsurgical group is 1:1). Considering a final follow-up rate of 80%, a minimum of 120 patients will be required for each group. There were approximately 25 patients undergoing surgery per year at our center; therefore, we plan to enroll the patients over the next 5 years. Since more patients are treated nonsurgically than surgically, all nonsurgical patients treated during the first 5 years will be enrolled.

The study duration is estimated to be 7 years to ensure that all recruited patients are followed up for 2 years. Each visit’s timeline and tasks are presented in Multimedia Appendix 1.

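### Progression-free survival is defined without death as an event, so the secondary endpoint is time to progression under a PFS label

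*Protocol article*

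**What the plan says.** Under Secondary Outcomes, the protocol article gives: "The progress-free survival period, defined as the time after the start of antitumor therapies until disease progression". The only event named is progression.

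The Primary Outcome section is explicit about death for the other survival endpoint: "OS is defined as the time after the start of any antitumor therapy for SMLC to death of any cause".

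Both endpoints receive the same analysis under Statistical Analysis: "The OS and progress-free survival curves will be plotted using the Kaplan-Meier method". For surgical against nonsurgical treatment, that section states that "a comparison of the two groups will be performed via the log-rank test".

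On timing, Study Design says "The patients will be visited postoperatively at 3, 6, 12, and 24 months", and Secondary Outcomes says that "secondary and other outcome metrics are assessed at each visit". The abstract adds that survival status is checked every 3 months. The article gives no censoring rule for PFS and no competing-risk method.

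**The concern.** PFS is understood as time alive and free of progression, so death ends it. The stated definition lets only progression end it. A patient who dies before any progression is recorded has plainly stopped being alive and progression-free, yet under the text does not fail.

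Two results are at stake. The first is the level of the PFS curve in each group. If these deaths are censored, Kaplan-Meier treats the patients as still able to progress later, and the curve sits too high for its label. Readers would then compare it with PFS from studies that count death. The second is the comparison of surgical with nonsurgical treatment. If deaths without recorded progression form a larger share of first events in one group, that group looks better on this endpoint because more of its failures are not counted.

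The article gives reason to expect some such deaths: assumed mean survival is 9 to 11 months, while the scheduled assessments leave gaps from 6 to 12 and from 12 to 24 months.

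**Working it through.** **1. The definitions side by side.** OS ends at death of any cause. PFS ends at progression. The article names death for OS and not for PFS, and no other section supplies it.

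**2. What the stated analysis does with a death.** Kaplan-Meier and the log-rank test use events and numbers at risk. With progression as the only event, a patient who dies first can leave the risk set only as a censoring, or be excluded. Censoring is inferred, since the article states no rule, but neither route counts the death as a failure. The formulas below are for censoring at death, the usual handling. Exclusion would select patients on their outcome, and these formulas do not describe it.

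**3. The plan's own figure.** The only power-based number concerns OS: "the average OS time was 11 (SD 4) months in the surgical group and 9 (SD 3) months in the nonsurgical group" and "Assuming an overall Type 1 error (α) of .05 and Type II error (β) of .1, we need 66 patients in each group".
- Pooled SD = sqrt((4² + 3²)/2) = sqrt(12.5) = 3.54; difference = 11 - 9 = 2 months.
- n per group = 2 × (1.960 + 1.282)² × 12.5 / 2² = 65.7, rounded up to 66. This reproduces with a two-sided α of 0.05 and 90% power. A one-sided α gives 54 and does not.
- PFS does not enter this figure, so changing its definition leaves it alone.

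**4. Effect on the PFS median (illustration).** Two inputs are assumptions because the documents give neither: the share s of first events that are deaths without recorded progression (10% to 50%), and the median m of time to progression or death (4 to 8 months). With constant hazards:
- total hazard = ln 2 / m
- progression hazard = (1 - s) × ln 2 / m
- Kaplan-Meier median when deaths are censored = m / (1 - s)

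| s | Factor 1/(1-s) | m = 4 | m = 6 | m = 8 |
|---|---|---|---|---|
| 10% | 1.11 | 4.4 | 6.7 | 8.9 |
| 20% | 1.25 | 5.0 | 7.5 | 10.0 |
| 30% | 1.43 | 5.7 | 8.6 | 11.4 |
| 40% | 1.67 | 6.7 | 10.0 | 13.3 |
| 50% | 2.00 | 8.0 | 12.0 | 16.0 |

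Entries are the median in months that the progression-only curve would show. A simulation of 400,000 patients with s = 30%, m = 6 and administrative censoring at 24 months gave 8.56 months (formula 8.57), against 6.00 for progression or death.

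**5. Effect on the group comparison (illustration).** Let both groups have the same hazard of progression or death, so the true PFS hazard ratio is 1. If the shares are a in one group and b in the other, the progression-only hazard ratio for the second against the first is (1 - b)/(1 - a):
- 20% and 30%: 0.70/0.80 = 0.875
- 20% and 40%: 0.60/0.80 = 0.75
- 10% and 30%: 0.70/0.90 = 0.78

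Each favours the group with more deaths without recorded progression. With equal shares the ratio stays at 1.

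**6. Are such deaths plausible?** Taking survival as roughly normal with the stated means and SDs (an assumption):
- Before 3 months: (3 - 11)/4 = -2 and (3 - 9)/3 = -2, so about 2% of each group die.
- Before 6 months: z = -1.25 (surgical) and -1 (nonsurgical), so about 11% and 16%.
- Between the 6- and 12-month visits: z from -1.25 to 0.25, about 49% (surgical), and from -1 to 1, about 68% (nonsurgical).

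Many deaths would fall in an interval without a scheduled assessment. This does not count deaths without recorded progression, because many of these patients may have progressed at or before 6 months.

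**The case against.** The strongest reply is that this is one clause in a condensed article. Censoring rules usually sit in the full protocol or SAP, and a label containing the word survival may be shorthand for the usual endpoint. That stands for the censoring rule: its absence here is no fault. It does not rescue the event definition, which the article does state, and which an SAP following it would carry forward.

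Other objections limit what can be claimed:

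- **Size.** A reader might fix on a single figure. For instance, a progression hazard of 1/8 per month with death hazards of 1/30 or 1/15 gives medians of 5.5 against 4.4 or 3.6 months, an excess of 27% to 53%. None of these hazards is in the documents. Constant hazards also fit the stated survival poorly: an exponential time has an SD equal to its mean, whereas the article gives SDs of 4 and 3 against means of 11 and 9, which points to a rising hazard and fewer early deaths.
- **Informative censoring.** A reader might take the illustration as proof of it. It is not. With independent constant hazards, Kaplan-Meier correctly estimates net time to progression, and the gap shown is between two endpoints. Dependence between death and disease state is plausible but not quantified here.
- **Frequency.** That many deaths will precede a recorded progression is not established. On the normal approximation, most patients would have two scheduled assessments before death.
- **Bias towards surgery.** A reader might infer this because postoperative deaths can occur only in the surgical group. The documents give no perioperative mortality. Patient Enrollment and Group Allocation also defines that group as patients who have surgery together with postoperative systemic treatment, so the earliest deaths may not enter the comparison at all. The direction of any differential effect is open.
- **Importance.** PFS is a secondary outcome. OS is correctly defined for death of any cause, and the sample size does not use PFS.

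**Conclusion.** The definition is wrong as written for its label: it describes time to progression. If deaths without recorded progression are censored, as the stated methods imply, the curve lies above PFS whenever any such death occurs. This direction needs no assumption about rates. The group comparison can also be distorted, but only if the share of such deaths differs between groups, and the documents do not say which way.

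The size is not determined by the documents. The range of 11% to 100% on the median rests on constant hazards and an assumed share of 10% to 50%; the apparent hazard ratios of 0.75 to 0.875 under a true ratio of 1 rest on assumed unequal shares. Both show how the error scales and do not predict the result.

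It should be fixed before analysis, but it does not undermine the study: the primary outcome and the 66 per group are untouched.

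**What to change.** Define PFS as the time from the start of antitumor therapy to the first documented progression or death from any cause, whichever comes first, and state that patients alive and progression-free are censored at their last assessment. Use that definition for the Kaplan-Meier curves and the log-rank test.

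If time to progression is also of interest, list it under its own name and report its cumulative incidence with death as a competing event.

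The cost is one sentence in the outcome definition, and one more if time to progression is kept. No new data are needed, because survival status is already checked every 3 months. Enrollment is planned to run to June 2027, so the change can be made well before analysis. The sample size does not change.

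### Pain relief and neurological recovery are compared between groups formed partly by pain and neurological deficit, with no baseline adjustment stated, so a comparison of improvement is likely to favour surgery

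*Protocol article*

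**What the plan says.** All places are in the Methods of the protocol article unless stated.

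- **Referral (Treatment).** The indications for surgery are "severe yet drug-resistant local pain, progressive neurological dysfunction, and emerging or latent spinal instability". The section continues: "Otherwise, patients are referred for nonsurgical treatment".
- **Eligibility (Patient Enrollment and Group Allocation).** The same criteria apply to both groups. Neither pain nor a neurological deficit is required for entry.
- **Outcomes (Secondary Outcomes).** Symptom recovery has two parts. One is pain relief, scored on the VAS. The other is described as "the recovery of neurological status, which is assessed using the American Spinal Injury Association (ASIA) score". Neither part is limited to patients who have the symptom at baseline. The section adds: "Immediate improvement in VAS and ASIA scores is assessed before discharge". Recovery of self-care on KPS and ECOG is a further outcome. Secondary outcomes are assessed at each visit.
- **Baseline data (Exposure Measures).** ASIA, VAS, KPS and ECOG are all collected.
- **Analysis (Statistical Analysis).** "The 1-tailed unpaired Student" *t* test and the chi-square or Fisher test "will be used to make comparisons between different groups". Multivariable modelling is named only as Cox regression, which serves the survival outcomes.
- **Stated biases (Discussion, Strengths and Limitations).** The remedies cover blinding of assessors and dropout. Selection on baseline symptoms is not mentioned.

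**The concern.** Two of the three surgical indications, drug-resistant pain and progressive neurological dysfunction, are also the conditions whose improvement is the outcome. What steers a patient into a group therefore also affects whether the outcome can occur. A patient who starts with a normal ASIA grade can only stay the same or worsen. A patient with little pain has little room for relief. Selecting patients on high pain also brings regression to the mean: part of their later fall in VAS would occur under any treatment.

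Adjusting the Cox model for overall survival does nothing for these outcomes. The Discussion expects the results to support a surgical strategy, and an unadjusted comparison of improvement would lean the same way. The stake is a claim that surgery relieves symptoms better, when the difference could come partly or wholly from who was referred.

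**Working it through.** **Plan's own figure.** The article gives no sample size or expected rate for symptom recovery. Its one reproducible figure concerns overall survival: (4² + 3²)(1.960 + 1.282)²/2² = 65.7, so 66 per group, as stated. The present point does not rest on it.

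**Inputs from the article.** 120 patients per group and a final follow-up rate of 80%, so 0.80 × 120 = 96 per group.

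**Assumed inputs.** The share of each group with a baseline neurological deficit, and a recovery chance of 50% among deficit patients in both groups, so that there is no true treatment difference.

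**Step 1: ASIA, share improved among all patients.**

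Observed share = (share with a deficit) × (recovery chance).

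Probability of a significant result ≈ Φ[(d − 1.96·se₀)/se₁], where d = p₁ − p₂, p̄ = (p₁ + p₂)/2, se₀ = √(2p̄(1 − p̄)/n) and se₁ = √([p₁(1 − p₁) + p₂(1 − p₂)]/n). With n = 96:

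- Deficits 30% vs 20%: 0.30 × 0.5 = 15% and 0.20 × 0.5 = 10%; se₀ = 0.0477, se₁ = 0.0476; Φ[(0.050 − 0.0936)/0.0476] = 0.18.
- Deficits 40% vs 15%: 20% and 7.5%; se₀ = 0.0497, se₁ = 0.0489; Φ[(0.125 − 0.0974)/0.0489] = 0.71.
- Deficits 50% vs 10%: 25% and 5%; se₀ = 0.0515, se₁ = 0.0495; Φ[(0.200 − 0.1010)/0.0495] = 0.98.

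Simulating the two-proportion test directly gives slightly higher values in the last two cases:

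| Deficit at baseline, surgical vs nonsurgical | Observed recovery | 96 per group | 120 per group |
|---|---|---|---|
| 30% vs 20% | 15% vs 10% | 18% | 21% |
| 40% vs 15% | 20% vs 7.5% | 73% | 82% |
| 50% vs 10% | 25% vs 5% | 99% | over 99% |

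The nominal rate is 5%, two-sided. The ranking can even reverse: with deficits in 60% vs 20%, a recovery chance of 30% with surgery against 50% without still shows 0.60 × 0.30 = 18% vs 0.20 × 0.50 = 10% improved.

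**Step 2: VAS, no treatment difference.** Assumptions: 100 per group, baseline mean 5 and SD 2, the same mean fall of 1.5 points in both groups, and baseline–follow-up correlation of 0.5 to 0.9. Patients go to surgery if baseline VAS exceeds 6, and otherwise with a chance of 25% or 50% for other reasons. Each setting had 1,000 runs. The baseline gap was 1.6 to 2.1 points.

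| Analysis | Result across settings |
|---|---|
| Change from baseline, unadjusted | 0.16 to 1.05 points of spurious extra relief with surgery; rejection 26–97% two-sided, 35–99% one-sided |
| Raw follow-up score, unadjusted | surgical group 0.8 to 1.9 points worse |
| Follow-up score adjusted for baseline | one-sided rejection 4–6% (nominal 5%) |

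**Step 3: after restriction.** Among patients with a deficit, equal recovery chances give equal observed shares (50% vs 50%) whatever the deficit split.

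**The case against.** The strongest reply is that the article does not fix the step on which the bias depends. It defines no responder, threshold or denominator for ASIA recovery. Recovery can be read as applying only to patients who have something to recover from, and the sentence on tests is generic. A fuller plan may settle this. That is fair as far as it goes. However, the article does state the outcomes without restriction, does name the tests, and confines multivariable adjustment to Cox models. Followed as written, that gives a biased comparison, which is more than an omitted detail.

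A reader might infer several stronger things that the documents do not support:

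- **That surgery is bound to look better.** The direction holds for change or share improved, which is what relief, recovery and improvement suggest. Raw follow-up scores would be biased against surgery, and progressive deficits may be less reversible.
- **That the groups split cleanly.** Instability alone is an indication for surgery, so some surgical patients may have no deficit and little pain. Stable deficits and milder or drug-responsive pain can remain in the nonsurgical group. Both narrow the gap without removing the mechanism.
- **That the false-positive rate is near 99%.** That is the top of a range set by assumed deficit shares; the mildest case gives 18%.
- **That the before-discharge reading does not exist for nonsurgical patients.** The article never says they are outpatients. What stands is that this reading has no common time point, because it depends on length of stay. A 3-month reading is already scheduled.
- **That deterioration goes unrecorded.** ASIA is taken at baseline and at each visit. Worsening is captured but is not named as an outcome.

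**Conclusion.** The point holds in limited form. Referral depends partly on pain and neurological dysfunction; improvement in both is an outcome for everyone; and only unadjusted tests are named for it. An unadjusted comparison of improvement is therefore likely to favour surgery when recovery among deficit patients is equal. A comparison of raw follow-up scores would be biased against surgery. Neither answers the question.

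For ASIA, the false-positive rate at a nominal two-sided 5% is about 18% to 99% with 96 per group. This rests on assumed deficit shares, an assumed equal 50% recovery and the planned 80% follow-up. For VAS, spurious extra relief of 0.16 to 1.05 points follows from assumed correlations and an assumed referral threshold. The mechanism comes from the text; the size cannot be known until baseline data are seen. The outcomes are secondary and the baseline measures are already collected, so this should be corrected but does not undermine the study as a whole.

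**What to change.** In Secondary Outcomes and Statistical Analysis:

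1. Analyse ASIA recovery among patients with a baseline deficit, stratified by or adjusted for baseline grade.
2. Compare VAS, KPS and ECOG at follow-up with adjustment for the baseline value, in place of an unadjusted test on change. A minimum baseline VAS alone would not remove regression to the mean.
3. Report ASIA deterioration among patients with a normal baseline grade.
4. Make the scheduled 3-month visit the first between-group comparison, and treat the before-discharge reading as descriptive.
5. Tabulate baseline ASIA and VAS by group. If few nonsurgical patients have a deficit, report recovery within groups only.

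This changes wording, denominators and models; it needs no new data and leaves treatment untouched. The cost is precision. If 10% of 120 nonsurgical patients have a deficit, the denominator is 12 before losses, and 6 of 12 recovering has a 95% interval of roughly 25% to 75%. Baseline adjustment also does not remove confounding by other factors that the multidisciplinary team weighs, so the adjusted comparison should still be reported as observational.
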